## Limitations

The symptoms of tic disorder are characterized by volatility. Its severity will be affected by life events, emotions, physical diseases such as infection and so on. Such fluctuations will affect our judgment of the treatment effect. To reduce misjudgment, we will use a scale related to life events and emotions in the evaluation and establish a 3-month follow-up period.

To ensure the quality of and effects obtained with this RCT, we will adopt a one-on-one treatment protocol. Due to the lack of therapists, our experiment will take a long time. In this process, participants will be required to come to the clinic at a fixed time every week. This may also result in the loss of these school-age participants. Online training and group therapy may be ways to solve this problem in the future.

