**Methods/design:**

We will perform a randomized control trial (RCT) to evaluate the efficacy and neural mechanisms of MHRT. The sample will include 160 participants (including 120 patients with TS and 40 healthy controls). The patient sample will be randomly divided into three groups exposed to three different types of training: MHRT, HRT, and psychoeducation and supportive therapy (PST). Participants will be assessed and undergo resting-state fMRI scans at baseline and at the end of the 12-week training. The Yale Global Tic Severity Scale (YGTSS) and Premonitory Urge for Tic Scale (PUTS) will be used to assess the severity of tic symptoms and premonitory urges. The primary outcomes are change scores on the YGTSS and other assessments from baseline and the end of the training. The secondary outcomes are the neural correlates of these trainings among these groups based on graph theory, which is used to characterize brain functional connectivity networks. The default mode network (DMN) and the salience network (SN) will be assessed (which have been associated with mindfulness as well as the generation of tic symptoms) by network parameters, including clustering coefficients and shortest path lengths. Changes in these network parameters will be regarded as the neural correlates of the behavioral training.

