### Assessment procedures

The clinical evaluation process will mainly be completed by two attending child psychiatrists. Before the formal evaluation, an evaluation of the consistency between raters will be completed. The clinical evaluation will be carried out only after the consistency of the raters is above 0.85. The time points for the evaluation mainly included the baseline test, within 1 week after the completion of eight sessions of intervention, and at the end of 1 month after eight sessions of intervention. The patients will be followed up at the end of 3 and 6 months after the eight sessions of intervention. For more details, see Figure 1.

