### Statistical analysis

Measures will be analyzed using IBM SPSS Statistics version 22 (IBM, Armonk, NY, United States).

First, the efficacy of MHRT will be tested using repeated measures analysis of variance (ANOVA). A 3 × 3 mixed design will be used to examine the main effects of group (MHRT, HRT or PST) as a between-subjects factor and time point as a within-subjects factor, as well as interaction effects. Second, for the imaging study, we will assess connectivity between the DMN and SN and compute the average Fisher r-to-z transformed Pearson correlations of the resting-state fMRI time-series between the nodes that belong to these resting-state networks. Pearson correlations will be used to replicate earlier functional connectivity studies. For analysis of the abovementioned neuroimaging indices, we will use univariate mixed-model analyses to assess the effects of MHRT and HRT. We will use the after-training outcomes as dependent variables, the group (MHRT, HRT, PST, and HC) as the independent variable and the baseline measure of the outcome as a covariate. We will also perform these analyses correcting for age, years of education and sex.

Measurement data will be presented as the mean ± standard deviation (x ± s). The demographic and efficacy indices of the three intervention groups before and after the intervention will be compared by multifactor analysis of variance (measurement data), and repeated measures analysis of variance and paired *t*-tests will be used for comparisons between multiple groups and before and after the intervention. In addition, we regarded at least 30% changes in YGTSS scores $\left[(\frac{\mathrm{Pr}e_{\left(YGTSS\right)}-Post_{\left(YGTSS\right)}}{\mathrm{Pr}e_{\left(YGTSS\right)}}\right)\times 100\%]$ as the clinically meaningful level.

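### Follow-up ends at 3 months in one section and 6 in another, the three-level efficacy model leaves out at least two of five visits, and the promised life-events scale is not among the instruments

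*Protocol article*

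**What the plan says.** The Limitations section of the protocol article describes tic severity as volatile and warns: "Such fluctuations will affect our judgment of the treatment effect". It then offers two safeguards: "we will use a scale related to life events and emotions in the evaluation and establish a 3-month follow-up period".

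Assessment procedures sets the visits. The evaluation points are "the baseline test, within 1 week after the completion of eight sessions of intervention, and at the end of 1 month after eight sessions of" the intervention. The next sentence adds two more: "The patients will be followed up at the end of 3 and 6 months after the eight sessions of intervention".

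Statistical analysis gives the efficacy model, a repeated measures ANOVA: "A 3 × 3 mixed design will be used to examine the main effects of group (MHRT, HRT or PST) as a between-subjects factor", with "time point as a within-subjects factor, as well as interaction effects". The three time levels are not named. The other efficacy tests in that section, including paired t-tests, compare values before and after the intervention. The Abstract fixes the primary window: "The primary outcomes are change scores on the YGTSS and other assessments from baseline and the end of the training".

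The Assessment instruments section describes eight measures one by one: Kiddie-SADS-L, YGTSS, PUTS, CY-BOCS, CGI, FFMQ, SCARED and the Wechsler scale. The legend of Figure 1 expands the same eight abbreviations.

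**The concern.** The protocol itself names fluctuation as a threat to judging the treatment effect and points to follow-up and a life-events scale as its answer. Neither is carried through consistently. The length of follow-up differs between two current sections, the efficacy model has fewer time levels than there are visits, and the life-events scale cannot be found among the instruments.

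What is at stake is durability. Session 7 of the MHRT training (Table 1) is about preventing relapse, and the protocol plans to see the children for months after the last session. Yet no stated analysis compares the arms at the later visits. A reader of the results could learn whether MHRT beats HRT or PST soon after training, but not, from any analysis the article describes, whether the difference is still there when follow-up ends.

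**Working it through.** No sample size, power or significance level is involved. The check is a count and a side-by-side reading.

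**1. Length of follow-up.** Limitations: 3 months. Assessment procedures: visits at 3 and 6 months, so the last is at 6. A 3-month visit exists in both, so the conflict is over where follow-up ends: 6 / 3 = a twofold difference. Both passages are current text.

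**2. Visits against model levels.**
- Evaluation points in Assessment procedures: baseline, within 1 week, 1 month = 3.
- Follow-up visits: 3 months, 6 months = 2.
- Total: 3 + 2 = 5.
- Time levels in Statistical analysis: 3.
- Visits outside the model, whichever three are chosen: 5 − 3 = 2.

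The plan's own figure of 3 is reproduced if the model holds only the three evaluation points. The model then stops at 1 month, and 6 − 1 = 5 of the 6 months of follow-up are not covered. The protocol does not say that these are the three levels, so the 5 months depend on that reading; the two omitted visits do not.

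**3. Whether another stated analysis uses the later visits.** The paired t-tests and the multifactor ANOVA are described as before-and-after comparisons. The mixed-model analyses with a baseline covariate are for the imaging indices and use the after-training value. The primary outcome ends with training. None clearly uses the 3-month visit, and none uses the 6-month visit.

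**4. Which tests randomisation protects.** A between-arm contrast at a given visit is protected: natural swings in tics fall on all three arms alike on average. A paired t-test within one arm is not, because a change over time in that arm contains any natural swing as well as any effect of training.

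**5. The life-events scale.** Of the eight listed instruments, none measures life events. On the emotional side SCARED measures anxiety, so that half of the promise is met in part. The events journals in Table 1 are MHRT session content, not an assessment made in every arm.

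**6. What modelling all five visits changes.** With 3 groups and T visits, time has T − 1 degrees of freedom and group-by-time has 2(T − 1).

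| | T = 3 | T = 5 |
|---|---|---|
| Cells | 9 | 15 |
| Time df | 2 | 4 |
| Group-by-time df | 4 | 8 |
| Within-subject error df, N = 120, no missing data: (120 − 3)(T − 1) | 234 | 468 |

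The last row assumes complete data. A standard repeated measures ANOVA drops any child who misses a visit. The protocol expects 20% dropout; if all of those children lacked at least one visit, 120 × 0.80 = 96 would remain, and each further visit required can only lower the number. Simply enlarging the ANOVA to 3 × 5 would therefore make this loss the same or worse.

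**The case against.** The strongest reply is that the 3 × 3 design need not be an error. Assessment procedures separates three evaluation points from two later follow-ups, and three points fit three levels exactly. An efficacy model confined to them, with longer follow-up analysed separately, is a legitimate choice, and that separate analysis may sit in a full protocol or analysis plan that is not shown. This stands as far as it goes: the three-level model is not wrong in itself. It does not settle the conflict over where follow-up ends, nor say which visits the three levels are, and the article's description of efficacy testing still contains no between-arm comparison at the later visits.

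A reader might infer something stronger: that a lasting benefit or a relapse cannot be told from a passing swing in tics. The documents do not support that. The children are randomised to three concurrent arms, assessors are blinded, and the group-by-time interaction is tested. Fluctuation adds variance but does not on average create a difference between arms. Visits at 1, 3 and 6 months are scheduled, so persistence can be examined if the data are analysed.

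A reader might also fault the protocol for having no measure of infection. Limitations mentions infection as a driver of tic severity but promises a scale only for life events and emotions, so no such promise is broken. Finally, Figure 1 is not available and its legend only expands abbreviations, so it cannot prove that a life-events scale is absent from the schedule. The instruments section, which describes even the IQ test in detail, is the firmer evidence.

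**Conclusion.** The point holds in a limited form. The end of follow-up is contradictory (3 against 6 months), at least two of five scheduled visits are outside the only longitudinal between-arm efficacy model, and the promised life-events measure is not identified. The consequence is that the stated analysis gives no between-arm result on whether benefit lasts to the end of follow-up, although the data are to be collected.

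The primary comparison from baseline to end of training is not invalidated. The within-arm paired t-tests lack the protection of randomisation and should not carry the efficacy claim.

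The count of two omitted visits needs no assumption beyond the visit schedule as printed. That the omitted visits are those at 3 and 6 months is the natural reading, not a stated fact. An analysis plan not shown could add a durability analysis, but it would not remove the conflict between the two sections of the article. The correction is worth making because it is cheap and turns data already planned into a result.

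**What to change.** - Reconcile Limitations and Assessment procedures on the length of follow-up.
- In Statistical analysis, replace the 3 × 3 repeated measures ANOVA with a likelihood-based mixed model of group by visit that includes every scheduled visit and keeps children who miss one. Do not simply extend the ANOVA to 3 × 5, which would drop those children.
- Keep the end-of-training contrast as primary. Report the MHRT–HRT and MHRT–PST differences at the follow-up visits, with confidence intervals, as the secondary durability result.
- Name the life-events instrument under Assessment instruments, or withdraw the promise in Limitations.

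The cost is protocol wording and slightly more analysis; no new visits are needed for the durability result. Intervals at the later visits will be wider because more data will be missing. If a life-events scale is in fact to be added, it brings a small extra burden at each visit.

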## Conclusion

The findings from this work will (1) provide evidence-based information on optimizing behavior therapy targeted at youth with TS. (2) The findings will shed light on the benefits of mindfulness in improving awareness and in reducing stress among children with TS. (3) The examination of brain networks will advance our understanding of the process underlying the pathogenesis of TS and how mindfulness works.

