However, based on some outcome studies, the efficacy of HRT still needs to be further investigated. A randomized control trial (RCT), in a comparison trial of HRT to exposure and response prevention (ERP), had results indicating that the ERP group experienced significantly greater reductions in tic severity (17). In another comparison trial, HRT and awareness training were compared, and participants in the HRT group experienced only a minimal benefit above awareness training (18). These studies showed that awareness training is an important component of HRT. Moreover, the treatment effects are also typically affected by age. Participants under the age of 10 may have difficulty learning awareness training due to difficulty with premonitory urge recognition (19). The key step of HRT is the detection of premonitory urges (PUs) (20), but insufficient awareness may lead to decreased curative effects, especially in younger individuals. Moreover, tics may be accompanied by emotional problems, such as anxiety and depression, but traditional HRT training does not adequately resolve these emotional problems. More improvements are needed to compensate for the limitations of HRT.

Mindfulness is attention to present moment experience without judgment, primarily to become reflectively aware of the nature of emotional and cognitive patterns based on a shift of emphasis from contents (e.g., of perceptions or thoughts) to processes (21). Mindfulness training shows salutary effects on cognition (increased awareness) and emotional wellbeing (improved mood and stress relief) in children and adolescents (22–24), which addresses the two problems of HRT. Therefore, we will attempt to integrate mindfulness into HRT and call the new therapy “mindfulness-based habitual reversal training” (MHRT). Improvements in the curative effects may be mainly based on two links: the first link is that mindfulness can enhance awareness of PUs; the second link is that mindfulness can alleviate the anxiety associated with tics during relaxation training (25).

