## Methods/design

### Participants

#### Recruitment of participants

Recruitment of TS patients will be from the Department of Psychiatry, Beijing Children's Hospital, where participants will have received a diagnosis of TS from an experienced multidisciplinary team including at least two attending psychiatrists using the diagnostic criteria in the DSM-5. The inclusion criteria were as follows: (1) 7–12 years old; (2) Chinese children's Wechsler intelligence test IQ ≥ 80; (3) first onset with no previous treatment; and (4) right-handed. The exclusion criteria were as follows: (1) diagnosed with other mental disorders, apart from obsessive–compulsive disorder (OCD) or attention deficit hyperactivity disorder (ADHD); (2) diagnosed with epilepsy or other neurological diseases (including craniocerebral trauma); (3) claustrophobia; and (4) metallic foreign objects in the body. The recruitment period was predefined for one and a half years (May 2022 to Dec 2023).

Recruitment of healthy controls will be from a primary school in Beijing. The inclusion criteria were as follows: (1) aged 7–12 years; (2) IQ ≥ 80; and (3) right-handed. The exclusion criteria were as follows: (1) diagnosed with neurological or mental diseases; (2) claustrophobia; and (3) metallic foreign objects in the body.

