#### Five facet mindfulness questionnaire

The FFMQ is a 39-item self-report measure (46) that is used to evaluate the internal perception of self-report to clarify the changes in subjective perception. The items on this scale focus on self-awareness of internal feelings, such as “when I walk, I deliberately pay attention to the feelings in physical movement”; or focus on emotions, such as “I focus on how my emotions affect my thoughts and behavior”.

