#### Screening child anxiety-related emotional disorders

The SCARED is a self-reported measurement tool specifically used to measure anxiety symptoms of children and adolescents, including the five factors of somatic/panic disorder, generalized anxiety disorder, separation anxiety disorder, social phobia, and school phobia, with a total of 41 items (47). The participants rated the frequency of each symptom on a 3-point scale of 0–2, and the average score of the relevant items was calculated as the specific anxiety symptom score and total anxiety score. Previous studies have shown that the scale has been widely used in the screening of children's anxiety and has good reliability and validity in the context of Chinese culture (48).

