## Discussion

This protocol describes a study assessing the efficacy of MHRT for children with TS and associated brain network mechanisms. To the best of our knowledge, this is an original intervention technology that may be valuable for the non-drug treatment of TS. The protocol was designed to investigate multiple aspects of the treatment response, not only tic severity but also the effects of MHRT, HRT and PST on psychosocial functioning and neural physiological mechanisms.

Our results may be consistent with previous studies in patients with TS that compared the effectiveness of HRT and PST in a similarly large sample of TS patients. Based on available pilot data, we predict that patients receiving MHRT or HRT may show significant and clinically meaningful reductions in tic severity compared with patients receiving PST. We speculate that augmenting HRT with mindfulness training will enhance tic severity reductions and result in stronger awareness and lower anxiety levels. The fMRI scans may show functional changes in brain networks associated with mindfulness.

Mindfulness training can improve performance in attention, working memory and cognitive control tasks (55–57). With the potential benefits of mindfulness in children with common neurodevelopmental disorders (58), more research has been conducted in recent years. In 2020, a study investigated the feasibility of a family-based mindfulness intervention in 100 attention-deficit/hyperactivity disorder (ADHD) children's families and found that the intervention group showed greater improvements in children's ADHD symptoms (59). In 2021, Muratori et al. in a 50-child sample of adolescents with ADHD and oppositional defiant disorders showed that participating in a mindfulness meditation was associated with a greater reduction in hyperactive behaviors in the school context (60). Another pilot study using mindfulness training for children aged 8–12 years with ADHD (*n* = 140) and their parents also showed promising results (61). A study in Hong Kong demonstrated the feasibility of a mindfulness program in the Chinese context (62). Accumulating evidence supports the applicability of mindfulness-based therapy for those with mental health and neurodevelopmental disorders. The theoretical basis suggests that it can also be beneficial for patients with TS.

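### The Conclusion promises evidence on stress, which no listed instrument measures; the emotional result the trial can give is on anxiety symptoms in children without a diagnosed anxiety or depressive disorder

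*Protocol article*

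**What the plan says.** The Conclusion of the protocol article states that the findings will "shed light on the benefits of mindfulness in improving awareness and in reducing stress among children with TS". The sentence names two benefits, awareness and stress, and one population, children with TS, without qualification.

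The emotional prediction in the Discussion is worded differently: adding mindfulness to HRT "will enhance tic severity reductions and result in stronger awareness and lower anxiety levels". That is anxiety, not stress.

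The section Assessment instruments gives a subsection to each of eight tools: Kiddie-SADS-L, YGTSS, PUTS, CY-BOCS, CGI, FFMQ, SCARED and the Wechsler scale. The Figure 1 legend lists the same eight. For anxiety, "The SCARED is a self-reported measurement tool specifically used to measure anxiety symptoms of children and adolescents". For awareness, the FFMQ is "used to evaluate the internal perception of self-report to clarify the changes in subjective perception".

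Under Recruitment of participants, a patient is excluded if "diagnosed with other mental disorders, apart from obsessive–compulsive disorder (OCD) or attention deficit hyperactivity disorder (ADHD"). Limitations adds that a scale on life events and emotions will be used, but does not name it. Its stated purpose is to reduce misjudgment of the treatment effect when tics fluctuate.

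**The concern.** A conclusion about a construct needs an outcome that measures it. The article announces a finding on stress and lists no stress outcome. If the plan is followed as written, the only dedicated emotional outcome at the end will be the SCARED anxiety score. Whoever writes the results must then either leave the stress claim without data or let an anxiety score stand in for it. The article itself does not treat the two as the same thing: the Background paragraph of the Abstract names stress and anxiety side by side.

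The second issue is the population. The Conclusion speaks of children with TS in general, but the exclusion criterion removes those with a diagnosed anxiety or depressive disorder. An anxiety result from this trial, in either direction, does not extend directly to them. A null result in particular would not rule out a benefit in the children with TS who are most anxious.

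**Working it through.** The article gives no figure on this point, so there is none to reproduce. The check is to match each claim with an instrument and with the enrolled population.

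**1. Constructs against instruments.**

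| Construct | Where claimed | Listed instrument |
|---|---|---|
| Awareness | Conclusion, Discussion | FFMQ; PUTS for premonitory urges |
| Anxiety | Discussion | SCARED |
| Stress | Conclusion | none (0 of 8) |

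The other listed tools do not fill the gap. The Kiddie-SADS-L assesses current and past disorders, the YGTSS rates tics, the CY-BOCS rates obsessions and compulsions, the CGI gives a global clinical impression, and the Wechsler scale gives IQ.

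**2. The scale in Limitations.** It appears neither among the instruments nor in the Figure 1 legend. Its stated role is to help interpret tic fluctuation. As written it is an aid to interpretation, not an outcome, so it cannot carry the stress claim unless the sponsor says that it should.

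**3. Population.** The criterion keeps OCD and ADHD and removes every other diagnosed mental disorder, which includes anxiety and depressive disorders. The SCARED result therefore belongs to children with TS without such a diagnosis.

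**4. Does the exclusion stop the SCARED from showing change?** The SCARED is a symptom score: "the average score of the relevant items was calculated as the specific anxiety symptom score and total anxiety score". No diagnosis is needed to score it, so symptoms below the diagnostic threshold can still change.

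The documents give no SCARED distribution and no share of children excluded, so any size is an assumption. As an illustration, suppose anxiety is normal, the top 20% to 40% are removed, relief is proportional to baseline, and the scale floor lies μ = 1.5 or 2.0 SD below the unselected mean.
- With c = z(0.80) or z(0.60), the mean falls by λ = φ(c)/Φ(c) = 0.350 or 0.644 SD. The SD becomes √(1 − cλ − λ²) = 0.764 or 0.650.
- The raw effect keeps a fraction (μ − λ)/μ. For 20% removed this is 0.767 (μ = 1.5) or 0.825 (μ = 2.0). For 40% removed it is 0.571 or 0.678.
- If the outcome SD shrinks with the baseline SD, the standardised effect relative to the unselected population is 0.767/0.764 = 1.00, 0.825/0.764 = 1.08, 0.571/0.650 = 0.88 and 0.678/0.650 = 1.04.

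The raw room to improve narrows. The standardised effect stays between 0.88 and 1.08 of its unselected value when both SDs shrink together, and falls to 0.57 to 0.83 only if the outcome SD is held fixed. The documents do not settle which applies. The exclusion therefore limits whom the result covers, and it does not make anxiety untestable.

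**5. Analysis of the SCARED.** Statistical analysis gives efficacy a 3 × 3 repeated measures ANOVA. For the imaging indices it already uses the after-training value with the baseline value as a covariate. For a two-arm comparison with equal variances at both visits and within-arm correlation ρ between them, the variance with baseline as a covariate is (1 − ρ²)/[2(1 − ρ)] = (1 + ρ)/2 of the variance of a change-score comparison. This is below 1 for any ρ below 1, so the adjustment costs no data and gains precision.

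**The case against.** The best defence has three parts. The sentence is a closing remark that promises to shed light, not an endpoint or a tested hypothesis. The hypothesis that matters, lower anxiety, has its instrument. And a condensed article may leave the details of the Limitations scale to a full protocol that is not shown. The first two parts stand and keep the point small. The third stands only in part: the article describes each instrument in turn and repeats the list in a figure legend, then announces a finding that none of them measures. That mismatch lies in what is stated, and if the unnamed scale is meant to resolve it, one line would say so.

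It is also fair that excluding other mental disorders is a legitimate choice of population. The objection is only to a claim written for a wider one. Baseline adjustment of the SCARED, for its part, supplies no stress measure and does not widen the population; it is a separate, free improvement.

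Three stronger readings are tempting, and the documents do not support them.
- A reader might infer that the lack of a depression severity scale undercuts the Conclusion as well. The Introduction does say that "tics may be accompanied by emotional problems, such as anxiety and depression, but traditional HRT training does not adequately resolve these emotional problems". But depression is rationale there; neither the Conclusion nor the Discussion's prediction claims an effect on it.
- A reader might infer that the whole sentence is unsupported. The awareness half is covered.
- A reader might infer that the exclusion pushes the SCARED to its floor and costs the trial its power. That would need an excluded share and a floor that the documents do not give, and an outcome SD held fixed while the baseline SD shrinks. It would also need an effect size for anxiety: the pilot effect of 0.68 under Sample size estimation was taken on the YGTSS. Exclusion is moreover by diagnosis, not by SCARED score, so a clean cut at the top is an extreme model.

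**Conclusion.** The point holds in limited form. One of the two benefits named in the Conclusion, stress, has no listed measure (0 of 8 instruments), and the unnamed scale in Limitations has another stated purpose. What the trial can support is a statement on awareness and one on self-reported anxiety symptoms, the latter in children with TS without a diagnosed anxiety or depressive disorder. This rests on the text alone, plus the plain reading that anxiety and depressive disorders fall under the exclusion of other mental disorders. It touches the wording of the claim and its population. It gives no ground for a statement about lost power, and the sample size is unaffected.

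**What to change.** 1. In the Conclusion, replace the stress clause with: *reducing self-reported anxiety symptoms (SCARED) in children with TS without a diagnosed anxiety or depressive disorder*. Alternatively, if the scale mentioned in Limitations is meant to carry the stress claim, name it, describe it under Assessment instruments and list it as an outcome.
2. Limit the anxiety prediction in the Discussion to the same population, and add that a null SCARED result would not rule out benefit in children with a diagnosed anxiety disorder.
3. Compare SCARED between the three randomised groups after training with baseline SCARED as a covariate, as Statistical analysis already does for the imaging indices.

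The first option under item 1 and items 2 and 3 need no new data: two changes of wording and a covariate already collected. The downside is a narrower claim. The alternative under item 1 keeps the stress claim, at the price of committing to a named scale as an outcome.
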